### Prospective study

Eligible patients who give written informed consent will be followed by OCT and other imaging modalities every 4 months to detect the earliest focal sites of disease progression. OCT, OCT-A and fundus autofluorescence imaging will be acquired using the Heidelberg spectralis retinal angiograph (Heidelberg Engineering Gmbh, Heidelberg, Germany). Adaptive optics imaging will be acquired via an RTX1 adaptive optics retinal camera (Imagine Eyes, Orsay, France). Microperimetry will be acquired via a Maia microperimeter (Centervue S.p.A, Padova, Italy). The trial schedule is shown in Table 2. Focal areas of change will trigger a targeted follow-up schedule to investigate the events at that focal area of change. Recruitment will take place across 12 different hospital sites: four main hospital sites Vienna, Basel, Southampton and Moorfields and 8 UK hospital referral sites feeding patients with focal events into the two UK main hospital sites (Southampton and Moorfields) for in-depth imaging. The 8 UK hospital referral sites are Bristol Eye Hospital, Guys Hospital, John Radcliffe Hospital, Princess Alexandra Hospital, Salisbury District Hospital, St Mary’s Hospital Isle of Wight, and St Mary’s Hospital London.

**Table 2 Tab2:** List of Measures Taken at Visits.

Procedures	Visit number (Month)										Focal event visits	
	1 (0)	2 (4)	3 (8)	4 (12)	5 (16)	6 (20)	7 (24)	8 (28)	9 (32)	10 (36)	1	2
Demographics	☑☑											
Medical history	☑☑											
Concomitant medications	☑☑											
Physical examination	☑☑											
Blood sample for DNA analysis	☑☑											
Ocular examination	☑☑			☑☑			☑☑			☑☑		
BCVA	☑☑			☑☑			☑☑			☑☑		
LLVA	☑☑			☑☑			☑☑			☑☑		
Colour fundus photography	☑☑			☑☑			☑☑			☑☑		
OCT	☑☑	☑☑	☑☑	☑☑	☑☑	☑☑	☑☑	☑☑	☑☑	☑☑	☑☑	☑☑
OCT-A	☑	☑	☑	☑	☑	☑	☑	☑	☑	☑	☑☑	☑☑
FAF	☑			☑			☑			☑	☑☑	☑☑
Adaptive optics	☑			☑			☑			☑		
Microperimetry	☑			☑			☑			☑	☑☑	☑☑
Adaptive optics at focal event visit											☑☑	☑☑

☑: Main site only.

☑☑: Main site & referral site.

*BCVA* best-corrected visual acuity, *LLVA* low luminance visual acuity, *FAF* fundus autofluorescence, *OCT* optical coherence tomography, *OCT-A* optical coherence tomography angiography.

All UK sites are secondary NHS Trusts with two further main sites located at University teaching hospitals in Basel and Vienna. In the UK, this study has been approved by the East Midlands - Leicester Central Research Ethics Committee (ref. 19/EM/0163); in Austria, by the ethics committee of the Medical University of Vienna; and in Switzerland by a national central research ethics committee, SWISSETHICS. The principles of Good Clinical Practice will be adhered to throughout in accordance with the Declaration of Helsinki.

Patients are informed about the planned number of visits and duration of their participation in the study as part of their informed consent. The trial schema showing the recruitment pathway, follow-up schedule and assessments of patients is shown in Fig. 1. Recruitment started in October 2019 and will end in June 2022. Follow-up will be a minimum of 2 years and maximum of 3 years.

**Fig. 1 Fig1:**
[figure not shown]
Pinnacle flow diagram.

## Outcomes

### Primary outcome

Relating to the fourth study objective, the primary endpoint for an individual participant is the occurrence of a focal event, defined as development of early-onset neurosensory atrophy or macular neovascularisation during the study. The primary analysis will be a Cox model of the time from baseline to either censored follow-up or to a primary endpoint. This analysis will provide the primary outcome of the study which is the identification of those particular candidate predictors (biomarkers and established risk factors) that remain important in the model, after backwards elimination, in jointly best predicting progression to a focal event. Key supportive outcomes, related to the understanding of this primary outcome, comprise: (a) the particular weighted combination, or relative importance, of these remaining important predictors; (b) corresponding with the model, an implied overall performance measure of the area under the ROC curve will also provide a range of estimates of sensitivity and specificity to demonstrate personalised predicted risk for individuals of progression to focal events; (c) the univariate performance of every candidate predictor will be transparently presented using sensitivity, specificity, and ROC curve where the biomarker is not a binary variable.

### Secondary outcomes

Sensitivity and specificity of novel imaging characteristics e.g. fundus autofluorescence (FAF), adaptive optics flood illumination ophthalmoscopy (AO-FIO), OCT-A at predicting disease progression; ROC curves; time from development of imaging change to development of these end-points; functional outcomes: BCVA, LLVA, microperimetry; structure-function correlation; structure-genotype correlation; predictive risk models.

### Exploratory outcomes

Within the prospective cohort of patients, in addition to the primary outcome we will record subsequent focal events and other AMD-related events which may occur any number of times during the follow-up period, in order to perform exploratory analysis of the progression to late AMD development.

## Study population for prospective study

### Inclusion criteria

Subjects 55–90 years old, with either intermediate AMD (as defined by ref. [27]) in both eyes, i.e. large drusen > 125 μm and/or any definite hyper- or hypopigmentary abnormalities associated with medium or large drusen; or intermediate AMD as defined above in one eye (study eye) and advanced AMD (geographic atrophy or choroidal neovascularization secondary to AMD) in the other eye.

Subjects should have media clarity and pupillary dilation for adequate imaging and functional tests.

Patients who are already taking part in a different study are able to consent to PINNACLE as long as it is safe to do so, and the data integrity of either study is not affected.

Exclusion criteria:Co-existent ocular disease, which might affect visual function or retinal morphology.Established glaucoma in either study eye or fellow eye with evidence of visual field loss or retinal nerve fibre loss (ocular hypertension is not an exclusion criterion unless associated with visual field loss or retinal nerve fibre loss in either eye).Cataract sufficient to affect retinal imaging.Myopia ≥ -6 dioptres or a history of myopia ≥ -6 dioptres if patient has had cataract/refractive surgery.Major ocular surgery 3 months prior or anticipated within the next 6 months following enrolment.Taking drugs known to cause retinal toxicity such as hydroxychloroquine or tamoxifen.In the study eye: OCT evidence of geographic atrophy (or complete RPE and outer retinal atrophy (cRORA)). This is (1) a region of hypertransmission of at least 250 μm in diameter, (2) a zone of attenuation or disruption of the RPE of at least 250 μm in diameter, (3) evidence of overlying photoreceptor degeneration, and (4) absence of scrolled RPE or other signs of an RPE tear.In the study eye: OCT evidence of choroidal neovascularization e.g. sub-retinal scar tissue, sub-retinal fluid or intra-retinal fluid associated with a pigment epithelial detachment.

### Harms and safety reporting

All serious adverse events (SAEs) occurring during the prospective study observed by the investigator or reported by the participant, will be noted on the CRF and reported to sponsor within 24 h of discovery.

The following information will be recorded: description, date of onset and end date, severity, assessment of relatedness to study, other suspect device and action taken. Follow-up information should be provided as necessary.

SAEs considered related to the study as judged by a medically qualified investigator or the sponsor will be followed until resolution or the event is considered stable. All related SAEs that result in a participant’s withdrawal from the study or are present at the end of the study, should be followed up until a satisfactory resolution occurs.

It will be left to the investigator’s clinical judgement whether or not a SAE is of sufficient severity to require the participant’s removal from the study. A participant may also voluntarily withdraw from study due to what he or she perceives as an intolerable SAE. If either of these occurs, the participant must undergo an end of study assessment and be given appropriate care under medical supervision until symptoms cease or the condition becomes stable.

The severity of events will be assessed on the following scale: 1 = mild, 2 = moderate, 3 = severe.

In addition to the reporting above, the CI shall submit an Annual Report to Leicester Central Research Ethics Committee who approved the study, which lists all SAEs that have occurred during the preceding 12 months.

### Recruitment

Patients will be recruited from participating hospital eye clinics. In addition, we will encourage community optometrists and patient charities to refer patients for participation.

### Consent

The participant must personally sign and date the latest approved version of the informed consent form before any study-specific procedures are performed.

Written versions of the participant information and Informed consent will be presented to the participants detailing no less than the exact nature of the study; the implications and constraints of the protocol; the known side effects and any risks involved in taking part. It will be clearly stated that the participant is free to withdraw from the study at any time for any reason without prejudice to future care, and with no obligation to give the reason for withdrawal.

The participant will be allowed as much time as wished to consider the information, and the opportunity to question members of the study team, their GP or other independent parties to decide whether they will participate in the study. Written Informed Consent will then be obtained by means of participant dated signature and dated signature of the person who presented and obtained the informed consent. The person who obtained the consent must be suitably qualified and experienced and have been authorised to do so by the Principal Investigator as detailed on the Delegation of Authority and Signature log for the study. The original signed form will be retained at the study site within the Trial Master File (TMF) or Investigator Site File (ISF). A copy of the signed Informed Consent will be given to participants and a copy retained in the participant medical notes.

### Prospective cohort analysis

We will conduct a prospective non-interventional study including 400 intermediate AMD patients (with 600 untreated intermediate AMD eyes, including both unilateral (AREDS IV) and bilateral (≥AREDS II)) over a minimum of 2 years to specifically investigate the morphological sequence of events preceding the conversion towards late AMD. All patients will be followed by OCT imaging every 4 months to detect the earliest focal sites of disease progression. As soon as focal areas of change (see below) are observed by the VRC, a targeted follow-up schedule will be triggered to investigate the events at that area of change in a targeted manner. 200 patients (main cohort) will undergo dense retinal phenotyping at 10 visits as per Fig. 1. Medical and smoking history, genotype and body mass index will also be included in the analysis. As well as structural tests, functional tests will be performed at baseline and yearly during the study using both microperimetry to identify focal changes and low luminance visual acuity to assess global changes. In case of focal progression, specific focal event microperimetry grids, which are tailored to the sites of progression, will be applied at all subsequent visits in order to functionally evaluate the morphological changes.

To increase sample size but make the study feasible an additional 200 patients at UK referral sites will undergo 4 monthly OCT and be referred to Southampton / Moorfields for dense phenotyping only if a focal event is detected by OCT (Fig. 1).

Signs of focal progression (as determined by the VRC) are defined as:focal drusen regression oroccurrence of novel nascent GA [28] ornew-onset PED, SRHM or intra- or subretinal fluid.

If signs of incipient focal progression (defined above) are observed, patients will undergo an intermediate visit within 2 weeks of the site being notified by the VRC and a second 4 weeks after that for targeted imaging and functional testing at sites of incipient focal progression including:AO camera to image photoreceptorshigh-resolution SD-OCT and fundus autofluorescence (FAF*) to image RPE.OCT angiography (OCT-A) to image choriocapillaris.Microperimetry (specific focal event and standard grids) to evaluate retinal sensitivity.

### Genotyping

For the prospective cohort, we will extract DNA from blood samples that will be genotyped on a Infinium Global Screening Array at the Advanced Genomics Biomedical Research Core Facility at the University of Michigan. Genotype data will be subjected to various quality control filters, likely resulting in a set of over 500,000 polymorphic variants. Principal components will be generated and used to adjust for population stratification. Ancestry will be estimated by projecting all genotyped samples into the space of the principal components of the Human Genome Diversity Project reference panel using PLINK [29]. Pairwise kinship will be assessed and used to reduce the data to a maximal subset that contained no pairs of individuals with 3rd-or closer degree relationship [30]. Additional genotypes will be obtained through imputation with the latest reference panels of the Michigan Imputation Server [31, 32]. We will calculate the same effect size weighted polygenic risk score (PRS) to identify patients at high risk for AMD in the UK Biobank component of the retrospective study.

### Microperimetry

The participants’ study eye will be tested for retinal sensitivity and fixation stability with the MAIA microperimetry (CentreVue, Padova, Italy) device. This machine presents Goldmann III stimuli with a dynamic range of 0–36 dB and a maximum luminance of 318.3 cd/m^2^ on a background of 1.3 cd/m^2^. Included real-time fundus imaging and eye-tracking provide a secure correspondence of light stimulus and retinal location during the examination. Three distinct grids will be employed throughout the study, which all feature a 4–2 thresholding strategy. (1) The 12-point training grid will be presented to the participants at the beginning of every MAIA examination. (2) The 24-point PINNACLE standard grid, which is centred in the fovea and covers the central 10-degree diameter circle, will be performed yearly. (3) The PINNACLE focal event grid features arrays of five points, tailored to the retinal loci of focal events. In case of focal progression, focal event grids will be designed by the site investigator and will be applied at all subsequent study visits. At the end of each examination the metrics of mean sensitivity, Bivariate Contour Ellipse Area (BCEA) fixation indices (63 and 95%) and percentage of fixation points within 1° and 2° of the foveal centre (P1 and P2) together with the sensitivity at every testing point will be exported for analysis.

### Features to minimise bias

Selection bias will be avoided by ensuring that all participants are recruited using the same recruitment strategy preferably in a consecutive manner and this ensures a representative sample from study sites over the study period. There is no randomisation or therefore allocation bias in this study. All images will be pseudonymised and sent to the Vienna Reading Centre, an established digital image analysis platform based on US Food and Drug Administration (FDA) and European Medicines Agency (EMA) standards, which has significant experience of reporting images based on standard operating procedures. This will avoid performance and detection bias. Being based on baseline visit data, candidate predictors are expected to be free from missing data. Any data would seldom be assumed missing completely at random, though a range of planned methods including ones intended for this assumption when missing data is infrequent, and ones for missing at random assumptions will be considered [33, 34], with sensitivity analysis undertaken. Being analysed with the Cox model which accommodates censored outcomes, none of the primary outcome data from those who drop out before study completion will be excluded from the analysis. This assumes data is missing at random conditional on the included candidate predictors, and sensitivity analysis will be undertaken. Candidate predictors and analyses will be listed in a statistical analysis plan specified before access to the joining of predictors and outcomes.

### Sample size

With 400 patients (600 eyes) we expect 170 composite time-to-event focal events signifying progression to late AMD. Focal events include drusen regression, early-onset neurosensory atrophy or choroidal neovascularisation, assuming 20% dropout and different 50%/20% unilateral/bilateral event rates, and conservatively maintained at 20% at the point of development of an event in the study eye(s) based on drusen regression in 26% of drusen over 5-year follow-up [35], and an overall conversion rate of 32% in unilateral neovascular AMD eyes over 2 years [35], which is in line with other literature [36]. Lifetable analysis showed that 170 events would be expected with these rates and 20% 3-year dropout. This was robust in a subsequent calculation over altered variable follow-up durations and employing higher observed event rates. For event modelling projects there is no statistical null hypothesis and so sample size calculations are not based on power. Instead, a rule of thumb is used that ten events (or ten non-events, if smaller) are needed per baseline-visit candidate predictor accommodated in the full model. Therefore, the initial model development stage after 360-eye follow-up (102 events) will accommodate ten identified structural biomarkers and potential genetic and phenotypic predictors. The 240-eye model (68 events) validation stage includes: calibration and discrimination and provides an informative narrow 95% confidence interval for C-index widths of ~±0.08.

### Plan for statistical analysis

The cohort will be divided 3:2 into a Cox model development stage (240 patients; 360 eyes; 102 primary endpoints) allowing ten (102/10) candidate predictors [33] and a validation stage (160 patients; 240 eyes; 68 primary endpoints), to enable the identification of the important predictors (primary study outcome) and their relative importance, and other key supportive outcomes including the area under the ROC curve with sensitivity and specificity estimates. After full recruitment, the patients defining these stages will be identified. Stage 1 modelling will begin prior to full follow-up. Candidate predictors will include identified structural biomarkers and potential genetic and phenotypic predictors. The initial full model will be a comparator and simplified with backwards elimination [37]. Continuous predictors will be included as fractional polynomials [38]. Models will include a unilateral/bilateral main effect to improve transportability to samples with an alternative case-mix. Intra-patient between-eye correlation will be accounted for with marginal models, with ‘eye’ the unit of prediction. Validation in Stage 2 will include calibration of the performance of the Stage 1 model [39] and discrimination via the C-index with sensitivity, specificity and predictive values, and assessment of any over-fitting bias.

External transportability of the model will involve meta-analytic methods. Fast progressors and early conversion to AMD will be explored, and short-term changes in predictors.

We will explore comparability of model parameters and C-indices in unilateral and bilateral subgroups, and composite constituents. We will follow approaches for modelling time-to-event data [33] and for external validation. The statistical analysis plan will be updated during the course of the study, for example: to record the definition of those biomarkers which are prioritised to be candidate predictors in the initial full model; to alter the number of candidate predictors that may be prioritised for accommodation in the full Cox model depending on the number of observed events achieved; to record any established risk factors that need to be initially assessed as candidate predictors; to handle missing baseline data in candidate predictors and over time in outcomes with sensitivity analysis; to record alternative methods should assumptions not be met; to record any secondary or exploratory additional analyses. These changes will be recorded within the final version of the statistical analysis plan which will be approved by the joint Trial Steering and Data Monitoring Committee (TSDC) prior to the joint access to both events and candidate predictors by the time of the final data lock.

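### The milestone for final SAP approval (final data lock) conflicts with a Stage 1 model fit that begins earlier, and the text does not say which time point governs

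*Protocol article*

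**What the plan says.** All references are to the protocol article.

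- **Features to minimise bias** sets the safeguard: "Candidate predictors and analyses will be listed in a statistical analysis plan specified before access to the joining of predictors and outcomes".
- **Plan for statistical analysis** splits the cohort 3:2 into development (240 patients, 360 eyes, 102 endpoints, ten candidates) and validation (160 patients, 240 eyes, 68 endpoints). On timing it says "After full recruitment, the patients defining these stages will be identified" and "Stage 1 modelling will begin prior to full follow-up".
- The same section adds that "The statistical analysis plan will be updated during the course of the study". The listed updates include defining the prioritised biomarkers, recording alternative methods if assumptions fail, and "to alter the number of candidate predictors that may be prioritised for accommodation in the full Cox model", the last depending on the number of events observed. The final version goes to the joint steering and data monitoring committee (TSDC) for approval "prior to the joint access to both events and candidate predictors by the time of the final data lock".
- **Sample size** places "the initial model development stage after 360-eye follow-up (102 events") and derives ten candidates from a rule of ten events per candidate.
- **Primary outcome** defines the study's primary result as the predictors still important after backwards elimination in the Cox model.

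**The concern.** A Cox model with backwards elimination cannot be fitted without a file that links each eye's predictors to its event time. Starting Stage 1 is therefore joint access for 60% of the patients. The approval sentence treats joint access and the final data lock as one moment, whereas the Stage 1 sentence puts joint access earlier.

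What is at stake is the primary result itself. The candidate list, its length and the fallback methods determine which predictors can be retained. If any of these is settled after a Stage 1 fit has been seen, the selection depends on the data and can no longer be called pre-specified. Validation in separate patients would expose optimism in calibration and discrimination, but it would not restore a pre-specified list.

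A second, smaller issue is size. The ten-candidate allowance rests on 102 development events, a count tied to completed follow-up of the 360 eyes. A model fitted earlier has fewer events.

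**Working it through.** **1. Order of events as written**

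| Step | Timing stated | Needs joined data? |
|---|---|---|
| SAP lists candidates and analyses | Before predictors and outcomes are joined | No |
| Stage membership identified | After full recruitment | No |
| Stage 1 modelling begins | Before full follow-up | Yes, for 240 of 400 patients |
| Final SAP approved by TSDC | Before joint access, by the final data lock | Should be no |

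If *before joint access* governs, approval must come before row 3. If *by the final data lock* governs, approval may come after row 3. The text supports either reading and contains no sentence tying approval to the start of Stage 1.

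**2. Which open items need joined data**

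- Number of candidates: depends on an event count, so no joining is needed. The final count, however, is known only when follow-up ends, after Stage 1 has begun.
- Biomarker definitions: can come from the retrospective dataset, so no joining is needed.
- Alternative methods if assumptions fail: checking proportional hazards needs joined data, unless the phrase means fallbacks written in advance.

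**3. The plan's own figures**

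- Split: 170 × 3/5 = 102 and 170 × 2/5 = 68. Candidates: 102/10 = 10.2, hence ten. These reproduce exactly.
- Eyes: 400 patients with 600 eyes means 200 unilateral eyes and 400 eyes in bilateral patients.
- Total events: reading 50% and 20% as 3-year rates (an assumption) with 20% dropout over 3 years, an annual life table with dropout after events gives 200 × 0.470 + 400 × 0.187 = 168.7, close to the stated 170. Continuous-time competing hazards give 162.8.

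**4. Development events at an early data cut (illustration)**

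Inputs: 60% of each group, so 120 unilateral and 240 bilateral eyes. Annual hazards are λ = −ln(0.5)/3 = 0.231 (unilateral), λ = −ln(0.8)/3 = 0.0744 (bilateral) and dropout μ = −ln(0.8)/3 = 0.0744. Each eye's event probability by follow-up t is λ/(λ+μ) × (1 − e^−(λ+μ)t). Follow-up is the time since entry, capped at 3 years. Recruitment from October 2019 to June 2022 is taken as 2.67 years with uniform entry.

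| Data cut | Development eyes drawn from all recruitment | Development eyes are the first 60% recruited (entry 0 to 1.6 years) |
|---|---|---|
| End of recruitment (2.67 y) | 49.7 | 67.9 |
| One year later (3.67 y) | 77.9 | 91.1 |
| All development eyes at 3 years | 97.7 | 97.7 |

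The last row is 120 × 0.454 + 240 × 0.180 = 54.5 + 43.2 = 97.7. The shortfall from 102 in that row belongs to this simple model and not to an early start. Under the ten-per-candidate rule, the early cuts support four to six candidates at the end of recruitment (49.7/10 to 67.9/10, rounded down) and seven to nine a year later (77.9/10 to 91.1/10).

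**The case against.** The strongest reply is that the plan already forbids what one might fear. Two sections require the SAP before predictors and outcomes are joined, and one of them does so without mentioning the data lock: "specified before access to the joining of predictors and outcomes". Read literally, that puts the final SAP ahead of Stage 1. This largely stands. A reader might infer that the plan permits predictors and methods to be changed after joining. The documents do not support that inference: no sentence authorises such a change, and altering the candidate number needs only an event count. What the reply does not remove is the approval sentence's own reference to the final data lock, which is wrong for the development patients whichever reading is preferred.

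A reader might also infer that 102 events is an error. That is not shown either. Full follow-up may mean follow-up of the whole cohort. If the earliest recruits form Stage 1, they could complete three years (about 4.6 years after the first entry) more than a year before the last recruits do (about 5.67 years). Beginning to model is not the same as making the final fit. The article says the event total was robust to altered follow-up durations, and it already allows the candidate number to follow the observed events.

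Finally, the full SAP may hold the sequencing detail. Missing detail is not the complaint here. The published text fixes two time points that do not fit together.

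**Conclusion.** The point holds as an internal conflict of timing. Joint access for 240 of the 400 patients begins with Stage 1, before full follow-up, while the sentence on final SAP approval places joint access at the final data lock. The plan does not say which governs, so the candidate list, candidate number and fallback methods could remain open after Stage 1 fits have been seen. There is no evidence that this is intended.

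The direct effect has no numerical size. The event figures illustrate only the second issue: about 50 to 68 development events at the end of recruitment and 78 to 91 one year later, against the stated 102. They rest on 3-year event rates, constant hazards, uniform entry, an assumed data cut and an assumed split rule, none of which the article fixes. They do not show that 102 is wrong for completed follow-up.

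This is worth correcting because it touches the primary outcome and cannot be repaired once Stage 1 data are joined. It falls short of a mandatory correction, because the intended safeguard is already stated twice and Stage 2 uses separate patients.

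**What to change.** In Plan for statistical analysis, replace the final-data-lock milestone with the following:

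1. The TSDC approves and dates the SAP version that fixes the candidate list, the candidate number (set from the event count alone), the stage split and the fallback rules before any Stage 1 file joins predictors to events.
2. Stage 2 predictors and outcomes stay unjoined until the Stage 1 model is frozen.
3. Any later change is logged and reported as post hoc.
4. Either the final Stage 1 fit is made once the development eyes have completed follow-up, or the candidate number is set from the events available at the Stage 1 data cut.

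The cost is wording, an earlier committee approval and possibly a later Stage 1 fit. No sample-size figure changes. If Stage 1 data have already been joined, state the date and the SAP version in force on that date, and treat everything settled afterwards as post hoc.
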